## Abstract

**Background:**

Employees dealing with job demands such as high workload and permeable work-life boundaries could benefit from bottom-up well-being strategies such as off-job crafting. We have developed a hybrid off-job crafting intervention to promote off-job crafting, a proactive pursuit to adjust one’s off-job time activities to satisfy one’s psychological needs. This hybrid intervention contains both on-site (two trainings) and online elements (smartphone app) to enhance employees’ well-being and performance within different life domains.

**Methods:**

The study is designed as a randomized controlled trial with an intervention group and a waitlist control group. The study population will be Finnish knowledge workers. The intervention program focuses on six psychological needs (detachment, relaxation, autonomy, mastery, meaning, and affiliation) proposed by the DRAMMA model. The intervention will consist of the following components: 1) an on-site off-job crafting training, 2) an individual off-job crafting plan for the four-week intervention period, 3) Everydaily smartphone app usage, and 4) a training session for reflection. The study outcomes are assessed with online questionnaires once at baseline, weekly during the intervention period and twice after the intervention (two-week and six-week follow-up). Moreover, during the second training session, participants will participate in a process evaluation to shed light on the mechanisms that can affect the effectiveness of the intervention.

**Discussion:**

We expect that the intervention will stimulate off-job crafting behaviors, which may in turn increase well-being and performance in both non-work and work domains during and after the intervention (compared to baseline and to the control group). The intervention may provide employees with additional resources to deal with various stressors in life. Furthermore, this off-job crafting intervention could also offer performance benefits for the employers such as increased organizational citizenship behaviors among employees.

**Trial registration:**

The Netherlands Trial Register (NTR): NL8219, December 9, 2019. Registered retrospectively. https://www.trialregister.nl/trial/8219

## Background

Demographic and economic changes have increased the need for employees to stay in the workforce longer than before, while also retaining high well-being and productivity. At the same time, the current workforce has to deal with job demands such as high workload and permeable work-life boundaries [1]. Excessive job demands can turn into stressors, which over time can lead to serious health outcomes, such as exhaustion [2]. This, in turn, can lead to negative consequences on the organizational level, such as increased absenteeism rates [3].

Scholars have proposed that employees dealing with high job demands could benefit from bottom-up well-being approaches [4, 5]. One of such approaches is job crafting, which refers to proactively adjusting one’s level of job demands and resources at work [6]. Although research has demonstrated that proactively adjusting one’s work activities to satisfy psychological needs can help employees to achieve higher well-being at work [7], limited research exists on the benefits of proactively adjusting one’s off-job time activities to satisfy psychological needs during non-work time, referred to as off-job crafting.

Within non-work domain, leisure crafting was first proposed as a concept different from mere participation in leisure activities [8], and later defined as “the proactive pursuit and enactment of leisure activities targeted at goal setting, human connection, learning and personal development” [9]. As people might engage in both recreational activities (e.g., sports, hobbies), and other non-work time activities (e.g., childcare, domestic tasks, volunteer work) to satisfy their psychological needs during the time they are not working, we refer to this form of crafting as off-job crafting. Off-job crafting may help to recover from stressful work because the demands on person’s psychophysiological systems are lower during that time and psychological resources can be replenished [10].

According to self-determination theory [11] all individuals have three innate psychological needs: autonomy, competence, and relatedness. Humans who actively seek out opportunities that satisfy these psychological needs will, in turn, experience positive psychological outcomes such as higher well-being [11] and performance [12]. More recently, Newman, Tay, and Diener [13] proposed a model of six psychological mechanisms mediating the relationship between leisure and subjective well-being. According to the DRAMMA model, these six psychological needs are: detachment, relaxation (referred to as “recovery” in the original model), autonomy, mastery, meaning, and affiliation. Detachment is characterized by mentally disengaging from work-related matters, while relaxation refers to low levels of mental or physical activation and little physical or intellectual effort [14]. Autonomy, one of the basic psychological needs proposed by Ryan and Deci [15], is the desire to experience ownership of one’s behavior. Mastery involves seeking learning opportunities and optimal challenges to experience feelings of achievement and competence [14]. Meaning refers to engaging in activities that individuals perceive as opportunities to gain something valuable in life [16]. Affiliation is the desire to experience relatedness and belongingness with other people [15].

Off-job crafting is primarily expected to satisfy psychological needs in non-work related life domains, but due to the universal nature of people’s basic psychological needs, it should also generate indirect spillover effects on work-related well-being and performance [17]. As there are significantly less -or even no- interfering job demands present during non-work time, people should be more effective in rebuilding their psychological resources via off-job crafting. This could ultimately also benefit people at work. We therefore propose that off-job crafting enhances employees’ well-being and performance both within the non-work domain as well as across life domains by the regeneration of psychological resources and satisfaction of psychological needs. To date and to the best of our knowledge, however, interventions to study whether off-job crafting yields these anticipated effects in terms of both well-being and performance in both life domains do not yet exist. We have therefore designed a hybrid off-job crafting intervention to stimulate off-job crafting among employees to enhance their psychological need satisfaction, well-being, and performance.

The aim of this intervention study is to evaluate the effectiveness of a hybrid off-job crafting intervention compared to a waitlist control group on off-job crafting behaviors, psychological need satisfaction, well-being and performance. We hypothesize that off-job crafting can be stimulated in the intervention group compared to a waitlist control group (between-person difference), and that people will engage more often in off-job crafting during and after the intervention period than before (within-person changes). Moreover, we expect that increased off-job crafting will lead to higher well-being and performance during and after the intervention (compared to baseline and to the control group). We hypothesize that as the result of the intervention, participants will report higher basic need satisfaction and satisfaction of psychological needs during and after the intervention compared to baseline and to the waitlist control group. In terms of work-related well-being outcomes, we expect that participants will report higher work engagement and job satisfaction during and after the intervention compared to baseline and to the waitlist control group. In the non-work domain, we hypothesize that participants will report higher subjective vitality, private life satisfaction and health status and lower stress and mental fatigue levels during and after the intervention compared to baseline and to the waitlist control group. We also expect the intervention to have a positive effect on both work-related and non-work performance. Namely, we expect participants to report higher job performance and organizational citizenship behavior at work and increased family role performance in the non-work domain during and after the intervention compared to baseline and to the waitlist control group. Additionally, we will explore, whether variables such as proactive personality, focus on opportunities, selection, optimization, and compensation strategies, need strengths, home and job demands, job crafting and off-job time activities have a role in participants’ engagement in different off-job crafting behaviors and its effects to their well-being and performance in different life domains.

The intervention development is partly based on the Intervention Mapping approach [18] which provides a stepwise process for developing evidence-based health promotion interventions. As a starting point, the planning group, consisting of researchers and well-being trainers, explored the needs and necessity of managing work-life balance and optimizing the use of leisure time, both theoretically and practically in the Finnish context. Recent studies [19, 20] have demonstrated that Finnish workers with knowledge-intensive jobs have difficulties to manage boundaries between work and non-work time. The advancements in mobile technology have made it possible for the employees to choose their work time and place. A study by Ropponen and colleagues [19] demonstrated that majority (79%) of employees felt the need to be available for the work all the time. According to the study conducted by Toivanen and colleagues [20], 42% of employees reported that they think about job-related matters often or rather often at home and only less than third reported feeling that they are well-recovered from work-related stress. Moreover, non-work time itself can also present people with different type of demands. Salmela-Aro and Upadyaya [21] showed that personal demands such as economic problems and taking care of dependents (e.g., children, elderly parents) vary across the lifespan of Finnish employees and are associated to work burnout. Based on the needs assessment, the following program objectives were formulated: increasing employees’ awareness of their psychological needs, and demands and resources both at work and in personal life; increasing awareness of off-job crafting possibilities; and stimulating off-job crafting behaviors among employees (including during breaks at work). We adapted the design of an existing job crafting intervention [22] to achieve these objectives. As part of the off-job crafting intervention, participants will (1) participate in two on-site trainings, (2) follow a self-composed off-job crafting plan, and (3) use the Everydaily smartphone app. The materials were pretested with a small group of students and adjusted based on their feedback. Before delivering the intervention, pilot testing of the program materials took place with employees from a target organization.

## Methods/design

### Study design

The effectiveness of the hybrid off-job crafting intervention will be evaluated using a two-armed randomized control trial with an intervention group and a waitlist control group. The study design is presented in Fig. 1.

**Fig. 1 Fig1:**
[figure not shown]
Off-job crafting intervention design

The study will be carried out in Finland from October 2019 to May 2020. All participants who have given informed consent to participate in the study will first fill out an online baseline questionnaire, concerning demographics (e.g., age, gender, education), basic job information (e.g., work hours), off-job and job crafting, psychological needs, well-being (e.g., mental fatigue, work engagement) and performance (e.g., family role performance, organizational citizenship behavior) 2 weeks before the intervention period. Additionally, intervention group participants will receive a small task to complete before the first training session. The task consists of composing a list of things that the participant likes and dislikes doing during their off-job time. In addition, they are asked to take two picture that represent: 1) an activity that they loved doing over the past week and 2) an activity that they did not like to do during their off-job time. One week before the first training session, participants will receive a reminder to complete the questionnaire and the homework task. Two weeks after the baseline measurement, intervention group participants will take part in a half-day long training session. Shortly before the training, each intervention group participant receives a personal feedback report containing information about their baseline scores on DRAMMA needs satisfaction and comparison of their scores to reference values derived from other published scientific studies with Finnish and European knowledge workers as the reference group [23–25]. During the four-week intervention period, every Tuesday, intervention group participants will receive an email with a link to a weekly online questionnaire. In case of non-response, reminders will be sent on Wednesdays and Thursdays. The control group will be asked to fill out a second questionnaire immediately after the end of the intervention period of the intervention group. Additionally, participants from both groups will receive the same online questionnaire via email twice during the post-intervention period (two and six weeks after intervention). After the intervention period, the intervention group will participate in a half-day long reflection session.

After the intervention, the waitlist control group will be offered a chance to participate in the trainings and all the intervention materials will be made available for them, including the booklet and Everydaily smartphone application.

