#### Basic analyses

All basic analyses are carried out with SPSS 25 [65]. Two-tailed significance level of < .05 will be considered statistically significant. Baseline characteristics of the participants are analyzed using descriptive statistics. Independent samples t-tests or chi-square tests are applied to check whether randomization was successful or whether there were systematic differences between the two groups. Preliminary analysis will be performed, including calculating descriptive statistics (i.e., means, standards deviations), factor analyses for all the scales, internal reliability calculations (Cronbach’s *α*) and bivariate correlations (Pearson’s *r*) between the study variables.

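### Homework goes to the intervention arm while baseline questionnaires are still being chased, so late intervention-arm baselines may be contaminated

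*Protocol article*

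**What the plan says.** The sequence is set out under Methods/design, Study design, in the text following Fig. 1.

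- Baseline comes first for everyone, two weeks before the intervention period: "All participants who have given informed consent to participate in the study will first fill out an online baseline questionnaire".
- One arm then gets something extra: "Additionally, intervention group participants will receive a small task to complete before the first training session". On its content: "The task consists of composing a list of things that the participant likes and dislikes doing during their off-job time". Participants also take two pictures, one of an off-job activity they loved and one of an activity they disliked.
- The chase-up is joint. A week ahead of the first training, "participants will receive a reminder to complete the questionnaire and the homework task".
- Training follows: "Two weeks after the baseline measurement, intervention group participants will take part in a half-day long training session".

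The Training sessions section uses the homework in the first session, as material for reflecting on need satisfaction and off-job activities. The Background lists raising awareness of off-job crafting possibilities among the programme objectives. The Effect evaluation section compares the arms on change in the outcomes over time. The Basic analyses section tests baseline differences in order to "check whether randomization was successful or whether there were systematic differences between the two groups".

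**The concern.** A baseline should be measured before either arm has received any part of its treatment. Here the homework is intervention content: it serves a stated programme objective and is worked on in the training. It asks people to review their off-job time, which is also what the off-job crafting scale and several other outcomes ask them to rate over the past week. Someone who does the task and then answers the baseline may rate themselves differently. Receiving the task also tells that person which arm they are likely to be in.

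This can happen in one arm only. Because effects are judged as change from baseline relative to control, an arm-specific shift at baseline carries into the estimated effect with opposite sign. It could also appear as a baseline difference in the planned t-tests and be mistaken for a fault of randomisation. The Strengths and limitations section discusses training materials leaking to controls but not this route.

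**Working it through.** **Timing.** Take the first training as week 0.

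| Event | Time | Arm |
|---|---|---|
| Baseline questionnaire, nominal date | week -2 | both |
| Homework sent | not dated, but before or with the reminder | intervention only |
| Reminder for questionnaire and homework | week -1 | outstanding items |
| First training | week 0 | intervention only |

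The reminder plans for baselines still missing at week -1, when the homework has been issued. A baseline answered at week -1 or later, with a one-week recall window, covers days after the nominal baseline date. Those days can include the homework. The personal feedback report is not a problem, because it is built from that participant's own baseline scores and so must follow them.

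**The plan's own figure.** The Sample size calculation gives an effect size of .25, two-sided alpha .05, power .80 and 64 per group. Read as Cohen's f for two groups, .25 equals d = 0.5. The t-test solution is 63.77, rounded up to 64 per group, so the figure reproduces. (Read as d, .25 would need about 253 per group.) The sample size is sound on this point and serves only as a yardstick.

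**Size of the bias.** Let p be the share of the intervention arm answering baseline after the homework, and s the shift in SD that those answers carry. Then

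bias in the between-arm change = -(p x s).

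The article gives neither p nor s, so both are assumed. The table shows p x s and, in brackets, the power at 64 per group if the shift works against a true d = 0.5. Power is calculated at d = 0.5 - p x s, taking the change score to have SD 1 (baseline-to-follow-up correlation 0.5). Without any shift it is 0.80.

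| | s = 0.1 | s = 0.2 | s = 0.3 |
|---|---|---|---|
| p = 0.10 | 0.01 (0.785) | 0.02 (0.769) | 0.03 (0.751) |
| p = 0.25 | 0.025 (0.760) | 0.05 (0.714) | 0.075 (0.665) |
| p = 0.50 | 0.05 (0.714) | 0.10 (0.612) | 0.15 (0.502) |

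Relative to d = 0.5, the range is 0.01/0.5 = 2% to 0.15/0.5 = 30%. If nobody is late, p = 0 and the bias is zero.

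**Direction.** On outcomes where higher is better, homework that raises baseline ratings makes the intervention's gain look smaller, which is conservative for the trial's hypothesis. Homework that lowers them makes the gain look larger. For stress and mental fatigue the signs reverse. Nothing in the article settles which applies.

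**Dependence on the model.** The one-for-one transfer holds for a simple baseline-to-follow-up contrast. As an illustration of a multilevel trend, assume linear time, equal weights and measurements at weeks -2, 1, 2, 3, 4, 6 and 10. The mean time is 24/7 = 3.43 and the sum of squared deviations is 87.7. A baseline-only shift then enters the intervention arm's slope with weight -5.43/87.7 = -0.062 per week. That is 0.74 of the shift over the full 12 weeks and 0.37 over the 6 weeks from baseline to week 4. A comparison of follow-up values that does not use baseline is not affected.

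**The case against.** The strongest reply is that the stated order is the right one. Everyone is to complete the baseline first, and the homework is described afterwards. Anyone who follows that order gives a clean baseline. The article does not say when participants are randomised or how they learn their arm. Fig. 1 is not available here, and a condensed article may leave such details to the full protocol. The task is also small, and some outcomes have no evident link to it: health status is rated as current general health, and listing liked activities need not change ratings of job performance. Finally, the baseline check in Basic analyses also looks for systematic differences in general, so it need not blame randomisation for a gap.

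All of that stands, and it limits the point to late responders. It does not remove it. The same paragraph that puts baseline first also plans a reminder for people who have not yet answered, when the task is already out in one arm. That is a feature of the stated sequence, not a detail left unsaid.

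A reader might go further and infer that the whole intervention-arm baseline is contaminated, that every change score is biased, or that false-positive rates are materially raised. The documents do not support this. It would require the shift to apply to the entire arm, whereas the mechanism reaches only the late share, and the direction is unknown. A reader might also infer that people who know their arm drop out before giving a baseline. That is possible, but nothing in the article shows it, and formal disclosure of the arm before baseline is itself an inference from who receives the task.

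**Conclusion.** The point holds in limited form. The protocol does not ensure that an intervention participant's baseline is complete before the homework arrives and the arm can be guessed, so late intervention-arm baselines may be contaminated. No control baseline can be answered after receiving the task.

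Under the assumed ranges (10% to 50% late, 0.1 to 0.3 SD per late responder), the average bias in a baseline-to-follow-up contrast is about 0.01 to 0.15 SD, in an undetermined direction. It is smaller if the model dilutes the baseline value and zero if nobody is late. The low end is negligible. The high end would matter, taking power from 0.80 to about 0.50 if it worked against a true d = 0.5. The size cannot be narrowed without the distribution of baseline submission dates. The case for acting rests on the asymmetry being avoidable at almost no cost, not on a demonstrated large bias.

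**What to change.** - Send the homework, and any notice of the arm, only once that person's baseline has been submitted.
- Send the questionnaire reminder to both arms in the same form, and send the homework reminder separately and only to those whose baseline is in.
- Record the submission date of every baseline. Where one was submitted after the homework was sent, flag it and run a sensitivity analysis without it. Applying the same calendar cut-off to controls in that organisation keeps prompt and late responders balanced between arms.

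The first two changes only re-order e-mails within the existing two-week window. The downside is slightly less time for the homework among people who answer late. For baselines already collected (the study period starts in October 2019), the third step is still possible if submission and homework dates were logged.

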### Strengths and limitations

The main limitation of the study is that the intervention includes several on- and offline components. With the two-armed randomized control trial (intervention versus waitlist control), it is not possible to evaluate each specific component separately, and it is therefore difficult to establish which intervention components are the most effective. However, we aim to conduct a thorough process evaluation to gain insights into recruitment, reach, fidelity, participants’ attitudes toward the intervention, context, implementation, dose delivered and dose received, and to link the effect and process evaluation results to better understand the different mechanisms that might have influenced the effectiveness of the intervention [34]. Secondly, as the intervention and the waitlist control group participants are recruited from the same organization and potentially form the same departments, contamination may occur. While the trainings, booklets and smartphone app are first only made available for the intervention group, there is still a chance that colleagues participating in the intervention could share their training materials with the waitlist control group participants. To minimize this risk, intervention participants are specifically reminded not to share the training materials with the control group members until the end of the intervention period. Thirdly, another limitation might be participants’ non-adherence to the instructions or dropping out of the study entirely. In order to avoid these potential complications, we will explain the procedures to the participants carefully both in the informed consent form and during the first training session to remind participants about the importance of following the entire intervention program. We will also send them a mid-intervention postcard reminder and will monitor closely the weekly questionnaire response rates, sending reminders to those who do not fill out the questionnaires by the deadlines indicated in the emails. We will further assess adherence to the intervention program with the process evaluation.

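### The no-sharing reminder lapses before the 2- and 6-week follow-ups, and nothing in the text holds waitlist access back until they are done, so the controlled follow-up contrast may be diluted

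*Protocol article*

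**What the plan says.** Four places in the protocol article bear on this.

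- **Study design, follow-up.** The programme lasts four weeks. Controls complete a questionnaire immediately after that period, and then "participants from both groups will receive the same online questionnaire via email twice during the post-intervention period (two and six weeks after intervention".
- **Study design, waitlist.** "After the intervention, the waitlist control group will be offered a chance to participate in the trainings". The same sentence releases the booklet and the app to controls. No date is given, and there is no reference to the last questionnaire.
- **Strengths and limitations.** The article names contamination as a limitation, because both arms come from the same organisation and possibly the same departments. The safeguard is that "intervention participants are specifically reminded not to share the training materials with the control group members until the end of the intervention period". The trainings, booklets and app are described as reserved for the intervention group only at first, again with no release date.
- **Background (aims) and Effect evaluation.** Effects on well-being and performance are hypothesised against the control group both during and after the intervention. The between-group analysis concerns change in outcomes across time.

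**The concern.** A waitlist arm serves as a control only while it remains untreated. Here the one safeguard with an explicit end point stops before both follow-ups. On its natural reading, the waitlist offer opens at the same moment. Colleagues could then pass on materials, and controls might start the programme itself, while they are still answering questionnaires meant to represent no intervention.

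The article describes three post-baseline questionnaires for controls: one at the end of the intervention period and two follow-ups. The two follow-ups are the ones that can show whether an effect lasts. If some controls benefit before then, the difference between arms shrinks, and a lasting effect could be mistaken for one that fades. Analysis cannot undo exposure that has already happened.

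**Working it through.** **1. Order of events.** Count the intervention period as weeks 0 to 4.

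| Event | Week | Basis |
|---|---|---|
| Control questionnaire at end of period | 4 | Study design, explicit |
| No-sharing request ends | 4 | Strengths and limitations, explicit |
| First follow-up, both arms | 4 + 2 = 6 | Study design, explicit |
| Second follow-up, both arms | 4 + 6 = 10 | Study design, explicit |
| Waitlist access opens | not dated; 4 on the natural reading | Study design |

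The natural reading rests on the preceding paragraph, which counts the follow-ups from the same reference point: "twice during the post-intervention period (two and six weeks after intervention". If access opened at week 4, controls could have up to 2 weeks of exposure at the first follow-up and up to 6 weeks at the second. The second figure exceeds the length of the four-week programme. The first is at most half of it.

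**2. The plan's own sample size.** Inputs from Sample size calculation and Basic analyses: effect size 0.25 (labelled medium), two-sided alpha 0.05, power 0.80, 64 per group. Reading 0.25 as Cohen's f for two groups gives d = 2 × 0.25 = 0.50.

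- Normal approximation: n = 2(1.960 + 0.842)² / 0.50² = 62.8, so 63 per group.
- Exact noncentral t: n = 64 per group, with power 0.801.

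The stated 64 is reproduced. Reading 0.25 as d would need 253 per group, so that is not what was meant.

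**3. Illustration of dilution.** Let c be the share of controls who gain the full effect before a follow-up. The document gives no value for c, so it is an assumption. The contrast becomes d = 0.50 × (1 − c). Power comes from a two-sample t test with noncentrality d√(n/2) and 2n − 2 degrees of freedom. The 100-per-arm column takes the recruitment target of at least 200, assumes a 1:1 split (the ratio is not stated) and assumes no loss.

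| c (assumed) | d | Power, 64 per arm | Power, 100 per arm |
|---|---|---|---|
| 0 | 0.50 | 0.80 | 0.94 |
| 10% | 0.45 | 0.71 | 0.89 |
| 25% | 0.375 | 0.56 | 0.75 |
| 50% | 0.25 | 0.29 | 0.42 |

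With some attrition from 200, the figures would lie between the two columns. The calculation treats one follow-up as a simple two-group comparison, whereas the plan uses multilevel models over time, so it shows direction and rough scale only.

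**The case against.** A reader might infer that waitlist access is fixed at the end of the intervention period and that the follow-ups become a comparison of two treated groups. The document does not support either.

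- **Timing.** The waitlist sentence has no date. Where the article means the exact end of the period, it says so, as it does for the control questionnaire. The section on study population and recruitment uses the same opening phrase for employer feedback that covers the different measurement points, which suggests a time after all measurements. Fig. 1, which may show the order, is not available here.
- **Route.** Colleagues can hand over a booklet. They cannot hand over two trainer-led sessions, a personal feedback report or an individual app access code. The explicit end point in Strengths and limitations concerns shared materials only.
- **Dose.** The training is offered and uptake is unknown. A control starting at week 4 could complete at most half of the four-week programme by the first follow-up, so assuming a full effect among exposed controls is severe.
- **Acknowledgement.** The article already lists contamination as a limitation.

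All of this tempers the size and certainty of the problem, but two things remain. The sharing request ends before both follow-ups however the waitlist sentence is read. And no text at hand delays access until the 6-week questionnaire. Acknowledging contamination does not help when the stated remedy stops short of the waves it should protect. Nor is this a detail usually left to an analysis plan, because it concerns trial conduct that the article itself describes.

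**Conclusion.** The concern holds in a limited form. The no-sharing request certainly lapses before the two controlled follow-ups. Waitlist access probably opens before them too, but that is a reading of an undated sentence and not a stated fact. Controls may therefore be partly exposed when persistence is tested, and the likely effect is dilution of the post-intervention contrast towards no difference.

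The loss could be small or serious. It depends on uptake and on how much benefit exposed controls gain, and the document gives neither. The tabulated power values assume full benefit in the exposed share and are illustrations, not estimates. The comparison from baseline to end of intervention is intact, because the control questionnaire immediately after the period comes before either release. The sample size of 64 per group is not in error on this point.

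This should be fixed. Confidence is medium, because the waitlist wording admits a later reading.

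**What to change.** Reconcile the two Study design statements (follow-up and waitlist access) with Strengths and limitations. State that waitlist access to the trainings, booklet and app opens only after the 6-week questionnaire is completed, and that the request not to share materials runs to the same point. Any instructions sent to participants should match.

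Where an organisation has already been promised earlier access, make the end-of-intervention wave the last randomised comparison there, and label later waves as uncontrolled.

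The cost is one sentence in each of the two places. Controls may wait up to about six weeks longer, and not at all longer if access was always meant to follow the last questionnaire.
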